## Abstract

**Introduction:**

Vertigo is a prevalent and burdensome symptom. More than 80% of patients with vertigo are primarily treated by their general practitioner (GP) and are never referred to a medical specialist. Despite this therapeutic responsibility, the GP’s diagnostic toolkit has serious limitations. All recommended tests lack empirical evidence, because a diagnostic accuracy study on vestibular disorders (‘How well does test x discriminate between patients with or without target condition y?’) has never been performed in general practice. The VERtigo DIagnosis study aims to fill this gap.

**Methods and analysis:**

We will perform a diagnostic accuracy study on vertigo of primary vestibular origin in general practice to assess the discriminative ability of history taking and physical examination. We will compare all index tests with a respective reference standard. We will focus on five target conditions that account for more than 95% of vertigo diagnoses in general practice: (1) benign paroxysmal positional vertigo, (2) vestibular neuritis, (3) Ménière’s disease, (4) vestibular migraine (VM) and (5) central causes other than VM. As these five target conditions have a different pathophysiology and lack one generally accepted gold standard, we will use consensus diagnosis as a construct reference standard. Data for each patient, including history, physical examination and additional tests as recommended by experts in an international Delphi procedure, will be recorded on a standardised form and independently reviewed by a neurologist and otorhinolaryngologist. For each patient, the reviewers have to decide about the presence/absence of each target condition. We will calculate sensitivity, specificity, predictive values, likelihood ratios and diagnostic ORs, followed by decision rules for each target condition.

**Ethics and dissemination:**

The study obtained approval from the Vrije Universiteit Medical Center Medical Ethical Review Committee (reference: 2022.0817—NL83111.029.22). We will publish our findings in peer-reviewed international journals.

**Trial registration number:**

ISRCTN97250704.

STRENGTHS AND LIMITATIONS OF THIS STUDYThe VERtigo DIagnosis study is a prospective diagnostic accuracy study that addresses the scientific gap of absent empirical evidence on the diagnostic value of history taking and physical examination for patients with vertigo in general practice.In order to improve the diagnostic toolkit of general practitioners, we will use data for individual diagnostic tests to construct easy-to-use diagnostic algorithms for the most prevalent causes of vertigo.Although this diagnostic accuracy study focuses on five target conditions—accounting for more than 95% of vertigo diagnoses in general practice, the study does not cover all possible causes of vertigo.

## Introduction

According to the International Classification of Vestibular Disorders (ICVD) of the Bárány Society, vertigo is “the sensation of self-motion when no self-motion is occurring or the sensation of distorted self-motion during an otherwise normal head movement”.^1 2^ It is a common symptom that increases with age, with a prevalence ranging from 5% in patients aged 18 or older to >30% in patients aged 75 or older.^3 4^ The burden of illness is substantial: four out of five patients with vertigo report severely impairing symptoms, leading to medical consultation, interruption of daily activities and/or avoidance of leaving the house.^4^ Moreover, medical consumption and decreased productivity form a large economic burden.^5^

Each year, a Dutch general practitioner (GP) with a standard practice list size (n=2095 patients) sees about 35 patients with vertigo and/or dizziness, of whom 17 patients with vertigo.^6^ More than 80% of patients experiencing vertigo in the Netherlands, the UK and the USA are primarily treated by their GP and are never referred to a medical specialist.^7–9^ The symptoms of these patients are predominantly caused by peripheral vestibular disease, like vestibular neuritis, benign paroxysmal positional vertigo (BPPV) or Ménière’s disease.^7 10^ Sometimes, vertigo in general practice is caused by vestibular migraine (VM)—a benign diagnosis most GPs are not familiar with.^11^ Incidentally, vertigo in general practice has a central and serious cause such as a cerebrovascular event.^7 10^ Despite the fact that GPs treat the large majority of patients with vertigo, their ‘diagnostic toolkit’ has serious limitations. First, there is no empirical evidence on the diagnostic value of history taking and physical examination for patients with vertigo in general practice, because diagnostic accuracy studies on conditions that may cause vertigo have never been performed in a primary care setting.^12 13^ Second, all recommendations for diagnostic testing in (inter)national guidelines are based on consensus and derivative suboptimal evidence from secondary and tertiary care.^6 14–18^ In particular, the quality of the empirical evidence for the recommended Dix-Hallpike manoeuvre is low due to selection bias (tertiary care patients not representative of patients seen in general practice), verification bias (only part of the study population received the reference test) and incorporation bias (reference test incorporates the result of the index test bias,^6 12 19–24^ while the quality of the empirical evidence for the recommended head impulse test is high but was performed among selected populations with patients not representative of general practice, leaving its value for GPs unclear.^6 12 19 25^

Furthermore, previous research suggests that GP diagnosis can be improved: GPs were able to provide a final diagnosis for 60%–64% of the older patients with vertigo/dizziness,^8 26^ whereas an expert panel could provide a diagnosis for 92% of the patients.^27^ Also, GPs hardly (1%–3%) diagnosed other contributory causes,^8 26^ whereas the panel identified other contributory causes in 46% of the patients.^27^

Finally, diagnostic errors sometimes have serious consequences. Whereas vertigo and dizziness are the symptoms most tightly linked to missed stroke, no less than 9% of cerebrovascular events are missed at initial emergency department presentation.^28^ Accurate and efficient diagnosis for these patients, although low-prevalent in primary care, may save lives and reduce costs through prompt and appropriate treatment.^29^

We hypothesise that the construction of a diagnostic algorithm for GPs may lead to faster and more targeted treatment, less diagnostic imaging and referral to the emergency department and/or hospital, less prescribing of antivertigo drugs and improvement of the overall outcome for patients with vertigo in general practice.

### Overarching VERtigo DIagnosis (VERDI) project

The VERDI project (also relating to Giuseppe Verdi, the Italian composer who experienced frequent episodes of vertigo and died of stroke) is a five-phase study. The current study is a study protocol for phase III of the VERDI study, that is, the diagnostic accuracy study (see figure 1). The design and objective of the other phases of VERDI are outlined below to explain the role of the current study within VERDI:

**Figure 1 F1:**
[figure not shown]
The five phases of the VERtigo DIagnosis project; the focus of the current study protocol, that is, the diagnostic accuracy study, is highlighted in red.

To assess and summarise the existing evidence on the accuracy of tests for diagnosing causes of vertigo in general practice (Systematic review);To determine which diagnostic tests should be investigated in a diagnostic accuracy study for patients with vertigo in general practice (Delphi Procedure);To investigate the diagnostic accuracy of history taking and physical examination for patients with vertigo in general practice (Diagnostic accuracy study);To construct an easy-to-use diagnostic algorithm for diagnosing causes of vertigo in general practice (Construction of diagnostic algorithm);To compare the diagnostic accuracy of GP judgement with the constructed diagnostic algorithm (Comparison study).

## Methods and analysis

### Aims and objectives

The main objective is to investigate the diagnostic accuracy of history taking and physical examination for patients with vertigo of primary vestibular origin in general practice.

### Study design

We will perform a prospective diagnostic accuracy study in general practice (‘How well does test x discriminate between patients with or without target condition y?’). Index tests include both questions during history taking (eg, ‘Is your vertigo accompanied by a headache?’) and diagnostic tests during the physical examination (eg, Dix-Hallpike manoeuvre). Target conditions: (1) BPPV, (2) vestibular neuritis, (3) Ménière’s disease, (4) VM and (5) central causes of vertigo other than VM. We will use the Standards for Reporting of Diagnostic Accuracy 2015 checklist to provide accurate and complete reporting of the results of our diagnostic accuracy study.^30^ Patient recruitment runs from March 2023 until February 2026; the overall study end date is 31 December 2027.

### Participants

We aim to recruit 960 patients from general practices in the Netherlands during 36 months (see figure 2). Eligible participants are adults aged 18 years and older presenting with vertigo—according to the definition of the ICVD of the Bárány Society^1 2^—in general practice. GPs are instructed to provide usual care, before, during and after enrolment of patients. At the end of a consultation, the GP will identify potential participants. The research team will approach potential participants by telephone and provide background information about the study, answer questions, check the eligibility criteria (see table 1), and, when the patient has the intention to participate, schedule an appointment for a home visit after 48 hours.

**Figure 2 F2:**
[figure not shown]
Flow chart of the VERtigo DIagnosis diagnostic accuracy study. GP, general practitioner; VNG, videonystagmography. *The estimated number of additional tests reported here (~10% for audiometry and ~30% for VNG) is based on additional analyses of the DIEP study. (Reported estimates reproduced from Maarsingh *et al*.^27^) DIEP, Dizziness In Elderly Patients study.

**Table 1 T1:** Inclusion and exclusion criteria

Inclusion criteria	Exclusion criteria
Aged 18 years and over	Serious comorbid conditions that preclude participation in the VERDI study (judgement of patient’s GP)
New episode of vertigo and/or episodic vestibular syndrome	Severe cognitive impairment (judgement of patient’s GP)
Presentation of symptoms during (telephone) consultation or home visit	Insufficient mastery of Dutch and English language

GP, general practitioner; VERDI, VERtigo DIagnosis.

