#### Index tests

The index tests under investigation (see table 3) will include all diagnostic tests that are recommended by the Dizziness Guideline of the Dutch College of GPs.^6^ This list of tests will be complemented with diagnostic tests for vertigo that were assessed during a systematic review (phase I VERDI) and were deemed appropriate for use in general practice by experts in an international Delphi procedure (phase II). During history taking, we will record sociodemographic characteristics (age, sex, education, partner status, cultural background), smoking habits, alcohol intake, current use of medication, medical history and vertigo characteristics (onset, duration, frequency, triggers, associated symptoms).^6^ Additionally, the patient will be asked to fill out the shortened version of the Dizziness Handicap Inventory (DHI-S), in order to investigate impairment due to vertigo.^33^

**Table 3 T3:** All index tests (history taking and physical examination)

**Sociodemographic characteristics**	**History taking**
*General patient characteristics*	*Vertigo characteristics*
Age	Onset
Sex	Duration
Education	Frequency
Partner status	Associated symptoms
Cultural background	Triggers
*Intoxications*	*Questionnaire*
Smoking habits	Shortened version of the Dizziness Handicap Inventory
Alcohol intake	
*Medical characteristics*	
Medication use	
Medical history	

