### Statistical analysis

#### Primary analysis: regression analysis and receiver operating characteristic (ROC) analysis

For each target condition, we will measure the amount of agreement between the outcome of (individual and combinations of) index tests and the consensus diagnosis. We will construct 2×2 tables to calculate sensitivity, specificity, prior probabilities, positive and negative predictive values, positive and negative likelihood ratios, and diagnostic ORs. Subsequently, we will perform multivariable logistic regression analysis with ‘presence or absence of target condition X, according to consensus diagnosis’ as dependent variable. Prior to multivariable regression analysis, we will perform univariate logistic regression analysis to investigate the associations between separate diagnostic indicators and the dependent variable. Variables will only be entered in the multivariable regression model if the univariate p value is <0.15. During multivariable analysis, we will follow the chronology in which investigations are performed in daily clinical practice.^46^ First, we will include all findings from history taking. This model will be reduced by (one by one) excluding variables with a likelihood p value of >0.10. Subsequently, we will add the results of physical examination (and possible other additional diagnostic tests) to quantify their added diagnostic value. Again, we will use a p value of >0.10 as cut-off to construct the final models. For each of the five target conditions (ie, (1) BPPV, (2) vestibular neuritis, (3) Ménière’s disease, (4) VM and (5) central causes other than VM), we will construct a final model and calculate sensitivity, specificity, predictive values, likelihood ratios, and diagnostic ORs.

After multivariable regression, in order to distinguish the discriminative ability (ie, the ability to discriminate patients with target condition X from patients without this target condition), an ROC curve will be constructed out for each target condition. An area under the curve (AUC) of 0.5 indicates no discrimination, whereas an AUC of 1.0 indicates perfect discrimination.^46^ We will test continuous variables for linear association with the outcome and we will use Spearman’s rank correlation coefficient to investigate multicollinearity.

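### Patients already diagnosed with a target condition can enter, and their medical history feeds both the model and the panel, so a prior diagnosis can help predict itself

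*Protocol article*

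**What the plan says.** **Entry.** The Participants section describes the population broadly: "Eligible participants are adults aged 18 years and older presenting with vertigo". Table 1 adds the criterion "New episode of vertigo and/or episodic vestibular syndrome". Its three exclusions concern comorbidity, cognition and language. None concerns an earlier vestibular diagnosis.

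**Index tests.** The Index tests section says that history taking will record, among other items, "current use of medication, medical history and vertigo characteristics". Table 3, captioned as the full list of index tests, includes medical history and medication use.

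**Model.** The Primary analysis section sets the order of modelling: "First, we will include all findings from history taking". The filters are statistical: "Variables will only be entered in the multivariable regression model if the univariate p value is <0.15", followed by removal of variables with p above 0.10. No exception is made for a prior diagnosis of the condition being modelled. Physical examination is added afterwards to quantify its added value.

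**Reference standard.** The panel members judge each condition from a form that includes the history, the examination and any additional tests.

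**Acknowledged limitation.** The Discussion concedes that the panel diagnosis depends on the index tests. The mitigation offered is clinical expertise and a 3-hour training.

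**The concern.** Take a patient with established Ménière's disease who consults for a further attack. The earlier diagnosis may appear under medical history, so it can be a predictor in the Ménière model. The panel sees the same entry when it decides whether Ménière's disease is present. The route from predictor to outcome then passes through the label as well as through the signs and symptoms of the present episode.

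This matters for two stated uses of the results. First, the Discussion justifies the later algorithm by the 36–40% of patients for whom GPs cannot give a diagnosis. An AUC pooled over known and unknown cases may be too favourable for that group. Second, physical examination is valued by what it adds after history, and the Discussion expects the models to show which tests might be dispensed with. A history model helped by an old label leaves less room for examination to show its worth.

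Training in performing and recording tests does not address this. Nor does the planned bootstrap, which corrects for overfitting.

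**Working it through.** The plan states no figure on this point, so there is none to reproduce. The textual chain is set out above. The calculation below shows only how large the effect could be.

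**Inputs from the article.** N = 960; prevalence 42% for BPPV and 10% for Ménière's disease (Sample size section). Expected cases: 0.42 × 960 = 403 and 0.10 × 960 = 96. VM prevalence is given as unknown.

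**Assumed inputs (not in the article).**
- f, the share of cases already carrying the diagnosis: 10% to 50%.
- g, the share of non-cases carrying the same old label: 2% to 5%.
- AUC of all other findings in undiagnosed patients: 0.70 or 0.80.
- Given case status, the label is independent of the other findings.

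**Step 1: the label as a single test.** LR+ = f/g, from 0.10/0.05 = 2 to 0.50/0.02 = 25. Diagnostic OR = [f/(1−f)]/[g/(1−g)], from 2.1 to 49.

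**Step 2: would it pass the univariate screen?** Expected z = (f−g)/√[f(1−f)/n₁ + g(1−g)/n₀]. For Ménière (n₁ = 96, n₀ = 864):
- f = 10%, g = 5%: 0.05/√(0.09/96 + 0.0475/864) = 1.6.
- f = 50%, g = 2%: 0.48/√(0.25/96 + 0.0196/864) = 9.4.

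For BPPV the range is 2.8 to 18.8. The p<0.15 threshold corresponds to z = 1.44, so in expectation the label enters, though only narrowly at the lowest Ménière setting.

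**Step 3: AUC with the label in the model.** The other findings were simulated as a normal score shifted by √2·Φ⁻¹(AUC) in cases, and combined optimally with the label (one million patients per setting).

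| f | Base 0.70 becomes | Base 0.80 becomes | Rise |
|---|---|---|---|
| 10% | 0.71–0.72 | 0.80–0.81 | 0.00–0.02 |
| 20% | 0.73–0.75 | 0.82–0.83 | 0.02–0.05 |
| 30% | 0.76–0.78 | 0.84–0.85 | 0.04–0.08 |
| 50% | 0.83–0.84 | 0.88–0.89 | 0.08–0.14 |

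Ranges run over g = 5% to 2%. BPPV and Ménière prevalences agree to within 0.005. Among patients without the label, the AUC stays at 0.70 or 0.80.

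**Step 4: added value of examination.** Read 0.70 as history alone and 0.80 as history plus examination, so the true gain in undiagnosed patients is 0.10. With the label in both models (BPPV, g = 2%), the gain becomes 0.810 − 0.718 = 0.092 at f = 10%, 0.849 − 0.778 = 0.071 at 30% and 0.890 − 0.840 = 0.050 at 50%. It shrinks but does not vanish.

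**The case against.** **Unstated detail.** An article need not say how medical history is coded or how a new episode is defined, and the full protocol or analysis plan may settle both. The word new might govern the whole entry criterion. Table 3 prints medical history and medication under a sociodemographic heading. These points leave real ambiguity. However, the Index tests section places both items within history taking, and an episodic syndrome is by nature recurrent. As written, the provisions allow the problem.

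**Legitimate information.** A GP knows the patient's history, and neither the objective nor the Participants section restricts the study to undiagnosed patients. Phase V compares the algorithm with GP judgement, which may use that history. This stands. It argues against excluding known cases or dropping the item from the main model, but not against reporting the undiagnosed group as well.

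**Panel behaviour.** A reader might infer that the panel will simply carry an old label forward. The documents do not say so. Two specialists judge independently, a third is brought in on disagreement, and patients with ear symptoms receive audiometry. Carry-forward is possible, not established.

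**Already admitted.** The Discussion acknowledges that the panel depends on index tests in general. It does not consider an index item that may be the diagnosis itself.

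**Conclusion.** The concern holds as a risk in the plan as written. A prior diagnosis can enter both the history model and the reference standard for the same condition, and nothing described separates patients who have one from those who do not. BPPV, Ménière's disease and VM are the conditions mainly exposed.

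The size is unknown. It is negligible if about 10% of cases are already diagnosed (0.00–0.02 in AUC) and material at 30% to 50% (0.04–0.14). These figures rest on assumed shares and on the label being independent of the other findings given case status. They compare the pooled result with the result in undiagnosed patients; they do not isolate how much the panel's access to the label contributes.

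Three stronger readings are not supported:
- **That the label discriminates almost perfectly.** Even if no non-case carried it, at 20% to 50% known its own AUC is (sensitivity + specificity)/2 = (0.20 + 1)/2 = 0.60 to (0.50 + 1)/2 = 0.75.
- **That accuracy is inflated throughout.** This self-prediction does not alter the 2×2 table of another single test, such as the Dix-Hallpike manoeuvre.
- **That the entry criteria are wrong.** They match the stated population.

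**What to change.** Keep the entry criteria and the full-population analysis. Then:

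1. For each target condition, identify whether it had been diagnosed before the present consultation, from the medical history already collected or, where that is not specific enough, from one additional case report form item.
2. State in the Primary analysis section that each condition's model is also fitted without a prior diagnosis of that condition, and treatment for it, as candidates.
3. State that accuracy and AUC are also reported in patients without a prior diagnosis of that condition, and that conclusions for undiagnosed patients about added value and dispensable tests are drawn from that analysis.
4. Add to the limitations that the panel still sees the label, because these steps do not remove that access.

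The cost is at most one form item per condition, a short addition to the analysis text and one extra table. The AUC may look less favourable, and the subset has fewer cases. For Ménière's disease, 96 expected cases fall to 86, 67 or 48 if 10%, 30% or 50% are already diagnosed (96 × 0.9, 0.7, 0.5). For BPPV, 403 fall to 363, 282 or 202. Estimates for Ménière's disease would therefore be noticeably less precise at the higher shares.

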### Home visit

After successful enrolment, participants will be investigated during a planned home visit by study physicians with clinical experience who received a 3-hour training aimed at optimally performing the index tests according to the current guidelines. During the home visit, the trained study physicians will record all clinical data using an electronic case report form (see the Data collection section). When the study physician has entered the results of the index tests, the electronic case report form will automatically provide an overview of indicated additional diagnostic tests for this individual patient according to the current guidelines.^1 11 25 29 31 32^ In case of symptoms that warrant immediate referral (ie, ‘red flags’ like diplopia, dysphagia, ataxia, facial weakness or numbness, see table 2),^6 19^ the study physician will instantly contact the principal investigator of the study. If necessary, the study physician will contact the participant’s GP to discuss further clinical management/immediate referral.

**Table 2 T2:** ‘Red flags’: serious conditions associated with acute vertigo and/or dizziness, for which GP assessment in the (very) short term or direct referral is necessary (the Dizziness Guideline of the Dutch College of GPs^6^)

Characteristics	Urgent condition(s)
Sudden dizziness with neurological symptoms, such as a combination of vertigo with dysarthria, diplopia, dysphagia or ataxia*; a paresis in one or both body halves, sensibility disorder in one or both body halves or homonymous hemianopia	Cerebral infarction, cerebral haemorrhage, transient ischaemic attack
Acute dizziness paired with simultaneously arisen acute *hearing loss*	Cerebral infarction, cerebral haemorrhage, transient ischaemic attack
Acute dizziness paired with acute, very severe headache or neck pain, whether or not after traumatic head injury	Subarachnoid haemorrhage, vertebral artery dissection
Lightheadedness paired with (almost) *falling/collapse* where a cardiac cause is suspected	(Serious) cardiac arrhythmias
Acute dizziness, headache, nausea, lethargy and prolonged stay in a closed room without ventilation	Carbon monoxide intoxication
Briefly existing dizziness in diabetes mellitus and abnormal behaviour or other indications of hypoglycaemia	Hypoglycaemia

*Extremity ataxia (abnormal finger-to-nose test, heel-to-shin test and diadochokinesis) is consistent with a central cause of dizziness. An abnormal (broad-based) gait pattern can occur with both central and vestibular causes and is therefore not distinctive.

GP, general practitioner.

